### Primary outcome

Physical capacity will be measured at baseline, three months, and six months with the 6MWT, recommended for measuring physical capacity [80, 86]. Further the Borg scale (6–20 scale) is used to obtain a subjective rate of perceived exertion during the test [87, 88], while HR is measured with a pulse oximeter before test start, after test end, one minute after test end, and two minutes after test end. 6MWT is an easy test with a low patient’s burden and is chosen due to its responsiveness, good validity for measuring physical capacity in people with PD, and clinical utility [86].

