### Sample size calculation

The primary outcome of the current study is the difference between groups in physical capacity, measured by the 6MWT. Previous studies among older adults have defined a substantial, meaningful change between groups in the 6MWT to be a mean (SD) of 50 (80) meters. This estimate requires 82 participants, 41 in each group, and a clinical trial with an independent comparison of two groups at a significance level of 0.05 and 80% power is assumed. Considering possible losses during follow-up, the sample will be expanded by 20% (20 participants). Thus, 100 participants will be included in total [113].

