### Statistical analyses

Results of the RCT will be reported following the CONSORT statement [114]. All statistical analysis will be conducted using the latest version of the SPSS and according to the intention to-treat principle (ITT). The normality of the distributions will be examined graphically by histograms and Q-Q plots, and by comparing the mean with the median. Descriptive data will be reported for variables of interest and reported as number (percent), mean (standard deviation) or median (25, 75 interquartile) based on what is appropriate. Between group differences at follow-up at three and six months after baseline will be assessed using linear mixed models for repeated measurements with a subject-specific random intercept. *P*-values < 0.005 will be considered statistically significant and all tests will be two sided. Effect size will be calculated (Cohen’s d).

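### No primary time point is named for the 6MWT, although it is compared between groups at both three and six months and the trial is sized for one comparison

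*Protocol article*

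**What the plan says.** The Primary outcome section lists three visits and ranks none: "Physical capacity will be measured at baseline, three months, and six months with the 6MWT". The abstract does the same for all measurements. The Sample size calculation defines the primary outcome without a visit: "The primary outcome of the current study is the difference between groups in physical capacity, measured by the 6MWT".

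That calculation rests on a "meaningful change between groups in the 6MWT to be a mean (SD) of 50 (80) meters", "at a significance level of 0.05 and 80% power is assumed", and concludes: "This estimate requires 82 participants, 41 in each group". It is a calculation for one comparison of two independent groups.

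Statistical analyses gives the planned comparison: "Between group differences at follow-up at three and six months after baseline will be assessed", by a linear mixed model with a random intercept per subject. It states no hierarchy between the visits, no joint test and no adjustment. It then sets the level: "values < 0.005 will be considered statistically significant and all tests will be two sided". That is one tenth of the level in the sample size paragraph, and no reason is given.

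Six months appears as the length of the programme (Background of the abstract, Design, Discussion), never as the primary time point.

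**The concern.** The time point is part of what defines a primary outcome. Here the 6MWT is compared between groups at two visits that the text treats alike, and nothing says which comparison decides the trial. An analyst who follows the article could report success on the primary outcome from whichever visit is significant.

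Two things are at stake. First, two looks at the same outcome, each at the full level, raise the chance of a false-positive primary claim above that level. Second, the aim is the effect of a six-month programme, so three months falls halfway through it. The Background notes that gains after supervised exercise tend to drift back toward baseline. A difference at three months that has gone by six months is therefore a realistic outcome, and the article does not say in advance how it would count.

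**Working it through.** **Inputs.** From the Sample size calculation: difference 50 m, SD 80 m, level 0.05, power 80%, 41 per arm. From Statistical analyses: level 0.005, two-sided tests, comparisons at three and six months. The correlation ρ between the two test statistics is not in the article; it is assumed, and a range is shown.

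**1. Reproduce the planned size.** n per arm = 2(z₁₋α/₂ + z₀.₈₀)² × SD² / difference². At a two-sided 0.05: 2 × (1.960 + 0.842)² × 80² / 50² = 2 × 7.85 × 2.56 = 40.2, rounded up to 41 per arm and 82 in total. This matches the article. A t-based calculation gives 41.2 per arm. Power at 41 per arm is 80.8% (normal) or 79.8% (t). The size therefore fits one test at 0.05.

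**2. Chance of at least one false positive over two visits.** This is 1 − P(|Z₁| < c and |Z₂| < c), with Z₁ and Z₂ bivariate normal with correlation ρ, c = 1.960 for 0.05 and c = 2.807 for 0.005.

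| ρ (assumed) | 0.05 per visit | 0.005 per visit |
|---|---|---|
| 0 (independent) | 9.75% | 1.00% |
| 0.5 | 9.1% | 0.96% |
| 0.7 | 8.3% | 0.90% |
| 0.8 | 7.8% | 0.85% |
| 0.9 | 7.0% | 0.76% |

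Over ρ from 0.9 to 0.5, the rate is 7.0/5 = 1.4 to 9.1/5 = 1.8 times the level at 0.05, and 0.76/0.5 = 1.5 to 0.96/0.5 = 1.9 times the level at 0.005.

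**3. Which ρ is plausible.** A random intercept implies equal correlation r between any two visits. The changes from baseline to three and to six months then have covariance SD²(1 − r) and variance 2SD²(1 − r) each, so they correlate at 0.5 whatever r is. That points to 9.1% at 0.05. If baseline is instead used as a covariate, the correlation is r/(1 + r). For r from 0.5 to 0.9 that is 0.33 to 0.47, and the rate is 9.5% to 9.1%. If the visits are compared without using baseline, ρ is r itself and may be higher, which gives the lower rates in the table.

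**4. The two stated levels.** At 0.005 the same formula gives 2 × (2.807 + 0.842)² × 2.56 = 68.2, so 69 per arm (70.1 by the t-based calculation) against the 41 stated. With 41 per arm the standardised difference is 50 / (80 × √(2/41)) = 2.83. Power is then Φ(2.83 − 2.807) = 51% (normal) or 48% (t). The stated 82 cannot be obtained at 0.005.

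**5. Keeping both visits primary.** Splitting the level as 0.025 per visit would need 49 (normal) to 50 (t) evaluable per arm for 80% power at each visit. The plan has 41, and power at 41 per arm would be 71% to 72%.

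**The case against.** The article condenses a fuller protocol, and testing order and multiplicity are commonly left to an analysis plan that is not shown. The sentence on group differences is general, covers all outcomes, and says only that they will be assessed within one model. The programme lasts six months, so a sensible reader would take six months as the main visit.

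Part of this stands. Three stronger readings that a reader might infer are not supported:

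- **That the trial's false-positive rate is 7% to 9%.** That figure needs 0.05 per visit. The analysis section itself sets 0.005, at which the rate is about 0.8% to 1.0%. The 0.005 may be a slip, since 82 reproduces only at 0.05, but the article does not settle it.
- **That significance at either visit counts as success.** No section says so. The text leaves that rule open; it does not adopt it.
- **That a result positive at three months and null at six could not be interpreted.** Given the programme length, it would naturally read as an effect not sustained to the end of the programme. The difficulty is that nothing fixes this reading beforehand.

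The objection does not remove the point. The visit belongs to the definition of the primary outcome, and the article defines that outcome in a section of its own and again in the sample size paragraph. Its analysis section is not silent either: it gives two comparisons where the sample size has one.

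**Conclusion.** The point holds in this form: the primary outcome has no primary time point, two visits are compared without order or adjustment, and the sample size supports one comparison. That much is read directly from the article.

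The size is conditional on the level that applies and on an assumed correlation of 0.9 to 0.5. It is about 7% to 9% against a nominal 5% if 0.05 applies, and about 0.8% to 1.0% against 0.5% if 0.005 applies. Both figures also assume that a significant result at either visit would be claimed as primary. The conflict between 0.05 and 0.005 is a separate inconsistency, and it matters more for power: about 80% under one level and about 50% under the other, with 41 per arm.

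This should be corrected. It does not call the design or the data collection into question.

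**What to change.** State that the single confirmatory comparison is the between-group difference in 6MWT at six months, the end of the programme, estimated from the mixed model. Report the three-month difference from the same model as secondary, with a confidence interval and no primary claim. Name six months in the Primary outcome and Sample size calculation sections as well.

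Reconcile the significance levels in Sample size calculation and Statistical analyses, and give one level with its reason. If 0.05 is meant, correct the 0.005; 41 per arm then stays adequate for the one six-month comparison. If 0.005 is deliberate, the sample size paragraph must be redone, since about 69 to 70 evaluable per arm would be needed for 80% power.

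The cost is a few sentences in three sections, with no change to visits or data, provided 0.05 is the intended level. The changes should be dated and made before any group comparison is seen. The one real downside is that an effect at three months alone can no longer support a primary claim.

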## Background

Parkinson’s disease (PD) is the fastest growing neurological disorder in the world [1]. It is a progressive and disabling disease with both motor and non-motor symptoms [2], potentially affecting several domains of a person’s life, including nutritional status [3, 4], health-related quality of life (HRQOL) [5], physical function and activity for daily living [6, 7].

It is known that physical activity and exercise can slow disease process and brain atrophy in PD, as well as delay symptom development [8], improve cognitive and physical function and capacity [9–12], and increase HRQOL [12–14]. Physical activity and exercise are closely related constructs but have different meanings, where the former is any bodily movement produced by the skeletal muscles resulting in energy expenditure, while the latter is intentional physical activity for improving health and fitness [15]. Due to the well-known effects of physical activity and exercise, they are key elements in today’s treatment guidelines and a combination of regular physical activity and exercise of moderate to high intensity is recommended [16]. Multiple forms of exercise are effective [8, 12, 17, 18], but have primarily short-term effect [19], and after a supervised exercise period, measures tend to return toward baseline values [12, 17, 20]. This regression may partly reflect the progressive nature of PD, but previous research suggests that maintaining motivation for exercise is difficult once formalised interventions end [20–24]. Experiences of poor health and disability symptoms may contribute to self-imposed activity restrictions and inactivity [25]. In addition, the experience of apathy, affecting the ability to initiate exercise, is a common non-motor symptom in PD [26]. Knowing the benefits of physical activity and exercise is not enough to change from a sedentary to an active lifestyle [27] and many people with PD remain sedentary [18, 28, 29].

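### The random-intercept model assumes one variance and one correlation across all visits; if correlation falls with time, the 6-month comparison can be anti-conservative, and an unstructured covariance would avoid this

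*Protocol article*

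**What the plan says.** The primary outcome is the 6-minute walk test at three fixed visits: "Physical capacity will be measured at baseline, three months, and six months with the 6MWT" (Primary outcome). For the analysis, "Between group differences at follow-up at three and six months after baseline will be assessed" with "linear mixed models for repeated measurements with a subject-specific random intercept" (Statistical analyses). No residual covariance structure, random slope or robust standard error is mentioned. The section does not say whether baseline enters as one of the repeated outcomes, as a covariate or not at all. Nor does it say whether the tested quantity is a change from baseline.

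The threshold in the same section is P "< 0.005 will be considered statistically significant and all tests will be two sided", whereas the Sample size calculation plans "at a significance level of 0.05 and 80% power is assumed". The two sections disagree, so results are given below at both levels.

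**The concern.** A subject random intercept with independent, constant-variance residuals implies compound symmetry. Every visit has the same variance, and the baseline-3, 3-6 and baseline-6 month correlations are all equal. In repeated measurements over months, the two visits furthest apart often correlate least. The model then averages short-interval and long-interval correlations and applies that average to the 6-month contrast. The standard error comes out too small, the confidence interval too narrow and the P-value too low. What is at stake is the error rate of the 6-month between-group comparison on the primary outcome.

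The setting gives some reason to doubt equal correlation. Baseline is taken at the end of an inpatient rehabilitation stay, the disease is progressive, and the article expects adherence and use of other care to differ between participants. With only three fixed visits, the restriction is also unnecessary.

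**Working it through.** **1. The plan's own figure.** The sample size uses "a mean (SD) of 50 (80) meters", two-sided 0.05 and 80% power. Per arm, 2 × (1.960 + 0.842)² × 80² / 50² = 40.2, rounded up to 41; this agrees with "This estimate requires 82 participants, 41 in each group". The calculation compares two independent groups and uses no between-visit correlation. The article therefore supplies none, and every correlation below is an assumption.

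**2. Change-from-baseline contrast at 6 months.** Take complete data and equal variances, with correlations in the order baseline-3, 3-6, baseline-6. The random-intercept fit estimates the within-subject error from the mean of the three correlations, so

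model SE / true SE = √[(1 − mean ρ) / (1 − ρ(baseline,6))],

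type I error = 2 × [1 − Φ(z × ratio)], with z = 1.960 at nominal 0.05 and 2.807 at nominal 0.005.

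Example with .85/.85/.75: mean ρ = .8167; ratio = √(.1833/.25) = .856; 1.960 × .856 = 1.678; type I error = .093.

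| Assumed correlations | SE ratio | Type I at 0.05 | Type I at 0.005 |
|---|---|---|---|
| .70/.70/.70 (equal) | 1.000 | .050 | .005 |
| .80/.80/.75 | .931 | .068 | .009 |
| .80/.80/.70 | .882 | .084 | .013 |
| .50/.50/.25 | .882 | .084 | .013 |
| .85/.85/.75 | .856 | .093 | .016 |
| .70/.70/.49 | .852 | .095 | .017 |
| .80/.80/.64 | .839 | .100 | .019 |
| .90/.90/.81 | .827 | .105 | .020 |

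Relative to nominal, this is 1.4 to 2.1 times at 0.05 and 1.8 to 4.0 times at 0.005. Simulation with 41 per arm and 40,000 runs per pattern agrees: .085, .095, .102 and .107 at nominal 0.05 for .50/.50/.25, .70/.70/.49, .80/.80/.64 and .90/.90/.81.

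**3. Baseline as a covariate, 3- and 6-month outcomes only.** Decay makes the two residual variances unequal, and the model pools them. With unit variances and a common baseline slope b = (ρ(baseline,3) + ρ(baseline,6))/2, the residual variance at a visit is 1 − 2bρ + b², where ρ is that visit's correlation with baseline. The SE ratio at 6 months is √(mean of the two variances / 6-month variance).

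- .80/.80/.75: b = .775; variances .361 and .438; ratio .955; type I error .061.
- .80/.80/.64: b = .72; variances .366 and .597; ratio .898; type I error .078. Simulation gave .085 (600 runs, Monte Carlo SE about .011).
- .90/.90/.81: b = .855; variances .192 and .346; ratio .882; type I error .084.

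**4. Other ways of handling baseline, at .80/.80/.64.** With baseline means constrained equal across arms, the type I error is .093. For a raw 6-month group difference with free baseline means and equal variances it is .050, so there is no inflation.

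**5. The 3-month change contrast.** In the decaying patterns above (all rows except the equal-correlation one), it errs the other way, with type I error about .025 to .041 at nominal 0.05.

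**6. Unstructured covariance.** For complete data this amounts to a t-test on the 6-month change. Simulated type I error was .051 to .053 at nominal 0.05 and .005 to .006 at nominal 0.005 for every pattern simulated, including equal correlations.

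**The case against.** The strongest reply is that the article fixes neither the correlations nor the contrast. This stands in part.

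- **Contrast.** The text speaks of group differences at 3 and 6 months without naming change from baseline or ranking the two visits. For a raw 6-month difference with equal variances, nothing goes wrong. A reader might infer that the planned analysis roughly doubles the type I error. The article does not support that as a general statement: doubling at nominal 0.05 is the upper end of an assumed range, for one way of setting up the contrast.
- **Evidence for decay.** The Background says that "after a supervised exercise period, measures tend to return toward baseline values". It is tempting to read this as evidence that correlation falls. It describes drift in average values, which the visit effect absorbs. Correlation falls only if individuals diverge. The article's remarks on variable adherence and care make that plausible but do not establish it.
- **Pattern.** If most change came soon after discharge, correlations such as .75/.85/.75 (also assumed) would give a ratio of √(.2167/.25) = .931 and a type I error of .068 for both the 3- and 6-month change contrasts. The 3-month test would then not be conservative. With baseline as a covariate there would be no inflation.
- **Unseen documents.** The text does not exclude a residual covariance structure added to the random intercept, and a fuller plan could specify one. The article nevertheless states a model, and a plan that follows its wording with default residuals carries the restriction forward. The point therefore concerns a stated choice, not something left out.
- **Recognised method.** A random-intercept model is an accepted analysis for three visits. That is true, but here its validity depends on a restriction that can be dropped at little cost.

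**Conclusion.** The point holds as a conditional weakness of the stated model. It does not show that the trial's results will be wrong. If correlation falls with time and residuals are independent with equal variance, the 6-month contrast is anti-conservative. For change from baseline the type I error is about 0.07 to 0.105 at nominal 0.05, or 0.009 to 0.020 at 0.005. For baseline as a covariate it is about 0.06 to 0.085 at nominal 0.05. The inflation is nil under equal correlations, and nil for a raw 6-month difference with equal variances and free baseline means. These sizes rest on assumed correlations and, for the formulas, on complete data. The percentages at 0.05 do not describe the decision rule as written; at 0.005 the absolute rates are lower but the relative inflation is larger. The change is worth making because it removes the dependence on an untested assumption.

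**What to change.** Replace the random intercept with an unstructured covariance over the fixed visits (SPSS MIXED: REPEATED visit, COVTYPE(UN)), using REML and Satterthwaite or Kenward-Roger degrees of freedom. Keep the random-intercept model only as the pre-stated fallback if the unstructured model does not converge. In the same sentence, state how baseline enters and which contrast is tested, since the size of the problem depends on both.

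The cost is wording plus a few variance parameters: six for three visits, or three if baseline is a covariate, with about 100 participants planned. If correlations are in fact equal, the loss is negligible. With 41 per arm and complete data, the error degrees of freedom for the change contrast fall from 160 to 80. The critical t value at 0.05 rises from 1.975 to 1.990, so the interval is about 0.8% wider (1.990/1.975 = 1.008). Design, sample size and conduct do not change.

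### Significance is declared only at P < 0.005 although the trial was sized at 0.05; under the stated rule, power for the primary outcome is about 47%, not 80%

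*Protocol article*

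**What the plan says.** Two sections of the protocol article's Methods fix a significance level, and they differ by a factor of ten.

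- **Sample size calculation.** The primary outcome is the between-group difference in the 6MWT. The target is "a mean (SD) of 50 (80) meters", and the calculation assumes "a clinical trial with an independent comparison of two groups at a significance level of 0.05 and 80% power is assumed". The result: "This estimate requires 82 participants, 41 in each group". This is raised to 100 to allow for losses, which the Abstract puts at an estimated 20%.
- **Statistical analyses.** Between-group differences at three and six months are to be estimated with a linear mixed model with a random intercept per participant. P-values below "0.005 will be considered statistically significant and all tests will be two sided".

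The second rule is not limited to secondary outcomes, is not described as a multiplicity adjustment, and carries no exception for the 6MWT. Nothing elsewhere in the article reconciles the two levels.

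**The concern.** The threshold decides whether the primary result is reported as positive or negative. If the Statistical analyses section is followed as written, the trial has roughly an even chance, or slightly less, of detecting the effect it was designed to detect, while the article claims 80%. If 0.005 is a slip for 0.05, the published decision rule for the primary outcome is wrong. Either level could then be cited as prespecified once the P-value is known. The two rules disagree over a range of results that includes the design target itself, so the ambiguity could settle the trial's conclusion.

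**Working it through.** **Inputs, all from the protocol article.** Difference δ = 50 m and SD σ = 80 m, so d = 50/80 = 0.625; α = 0.05 and power 80% (Sample size calculation); two-sided tests and the 0.005 threshold (Statistical analyses); 1:1 allocation (Randomisation); 20% dropout (Abstract). With 100 randomised, 20% dropout leaves 80, or 40 per arm.

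**1. Reproduce the plan's figure.** Normal approximation, per arm:

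n = 2 × [(z₁₋α/₂ + z₁₋β) × σ/δ]²

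At two-sided 0.05: 2 × [(1.960 + 0.842) × 1.6]² = 40.2, rounded up to 41 per arm, 82 in total. This matches exactly. A one-sided test would give 32 per arm. The sample size was therefore computed at two-sided 0.05.

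**2. Power at each threshold.** The standard error is SE = σ√(2/n): 17.67 m at 41 per arm, 17.89 m at 40 and 16.00 m at 50. The normal approximation is Φ(δ/SE − z₁₋α/₂). The t-test figure uses the noncentral t distribution with 2n − 2 degrees of freedom and noncentrality δ/SE.

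| Per arm | α = 0.05, t | α = 0.05, normal | α = 0.005, t | α = 0.005, normal |
|---|---|---|---|---|
| 40 (after 20% dropout) | 78.8% | 79.8% | 46.7% | 49.5% |
| 41 (as stated) | 79.8% | 80.8% | 48.1% | 50.9% |
| 50 (no dropout) | 87.2% | 87.8% | 60.1% | 62.5% |

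At 40 or 41 per arm the loss is about 30 to 32 percentage points by either method.

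**3. Smallest observed difference that would be significant, 40 per arm (t, 78 df).**

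- α = 0.05: 1.991 × 17.89 = 35.6 m
- α = 0.005: 2.889 × 17.89 = 51.7 m

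An observed 50 m gives t = 50/17.89 = 2.795, P = 0.0065: significant under the first rule, not under the second. Any observed difference between about 36 m and 52 m would lead to opposite conclusions.

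**4. Size needed for 80% power at 0.005.** Normal approximation: 2 × [(2.807 + 0.842) × 1.6]² = 68.2, so 69 per arm. By t-test, 70 per arm gives 79.9%, so 71 are needed. That is 138 to 142 completers; 138/0.8 = 172.5, so at least 173 randomised, against the planned 100.

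**The case against.** **It is probably a misprint.** That is plausible: no reason is given for 0.005, and the sample size uses 0.05. If so, no power is lost, and the power figures are conditional on 0.005 being applied. But a reader cannot be sure, because the trial has many secondary measures and a stricter level could have been deliberate. The text as published states the wrong rule in one place or the other.

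**The 47% changes method and number at once.** The plan's 80% belongs to 41 per arm under the normal approximation, and the like-for-like figure at 0.005 is 50.9%. The 46.7% uses the t-test with the completers expected after dropout. Both are legitimate, and 47–51% is the fair range.

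**The planned analysis is a mixed model, not a t-test.** This is the strongest point. If 80 m is the SD at a single time point, and if the model makes use of baseline, the effective SD is 80√(1 − r²), where r is the correlation between baseline and follow-up. The article gives neither fact. With 40 per arm at 0.005 (t-test):

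| Assumed r | Power | Smallest significant difference |
|---|---|---|
| 0.3 | 52% | 49.3 m |
| 0.5 | 63% | 44.8 m |
| 0.7 | 84% | 36.9 m |

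So the statement that an observed 50 m would miss significance depends on the simple comparison and already reverses at r = 0.3. Restoring 80% power needs r of about 0.65 or more. If 80 m is already the SD of change, most of this gain disappears. The article's own claim of 80% rests on the simple two-group comparison, and on that basis it fails at 0.005.

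**The sample size arithmetic is correct.** True. The defect is a contradiction between two sections; the arithmetic shows only what the contradiction costs.

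**Conclusion.** The concern holds. The article gives two incompatible significance levels for its primary outcome, and the stated 80% power belongs only to 0.05. Under the 0.005 rule as written, power for 50 m is about 47% (t-test, 40 completers per arm), and at most about 51% on the plan's own method and 41 per arm. Even with no dropout it is only about 60% (t-test). These figures assume SD 80 m and the simple two-group comparison on which the plan bases its sample size. A baseline-adjusted mixed model could recover part or all of the loss, but only under a correlation that the article does not give. Because the threshold determines the primary conclusion, this must be corrected whether 0.005 is a misprint or intended.

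**What to change.** In Statistical analyses, state that the primary 6MWT contrast is tested two-sided at 0.05, as in the sample size calculation. If 0.005 was meant as protection against many secondary tests, say so and confine it explicitly to the secondary outcomes.

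If 0.005 is to stand for the primary outcome, the Sample size calculation must instead give the power at that level: about 47% for the two-group comparison after dropout, or a figure for the mixed model with its assumed correlation stated. Re-sizing at 0.005 would need at least 173 randomised. That is unlikely to be practical, since the Results section planned for recruitment to finish around January 2023.

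The decision should be dated and made before any unblinded outcome data are examined. Setting the primary threshold to 0.05, or restating the power, costs one sentence in the protocol and analysis plan plus a published correction, and no additional participants.
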